#### Physiological assessment

2.4.2

Heart rate variability (HRV) will be monitored continuously throughout each listening intervention and pain stimuli procedure. HRV, the variation in time between consecutive heartbeats, can be used as a marker for autonomic function [47,48]. An increase in HRV can be seen due to activation of the parasympathetic nervous system, causing relaxation and recovery [49]. This effect can also be seen when listening to music [50]. HRV will be measured using an Acentas Chest Strap (BM innovations GmbH), providing an objective measure of the physiological response to the interventions [51].

#### Psychological questionnaires

2.4.3

In addition to the objective pain endurance, as measured in amperage, participants will be asked to rate the pain intensity and pain unpleasantness using an 11-point Numeric rating scale (NRS), where 0 implies no pain and where 10 implies the worst pain imaginable [52]. Since pain is a highly subjective experience, measuring (changes in) emotions is essential in pain assessment [53]. Anxiety will be measured with the State-Trait Anxiety Inventory (STAI-6) at baseline and after each intervention [54,55]. This questionnaire consists of six items and is a validated and frequently used method (Cronbach's α 0.83) [56]. Furthermore, the participants' emotions will be assessed with the Self-Assessment Manikin (SAM) at baseline and after each intervention. The SAM is a validated non-verbal pictorial assessment technique that directly assesses the emotional valence (Cronbach's α 0.73) and arousal (Cronbach's α 0.98) associated with a person's affective response to a wide variety of stimuli [57,58]. Moreover, the personal experience of listening to music and the podcast will be evaluated at the end of the experiment with five open-ended questions. This evaluation aims to account for confounders and to elaborate upon any interaction(s) between personal experience, music perception and pain endurance.

#### Socio-cultural background

2.4.4

This study will assess socio-cultural background of participants with validated sociological questionnaires, focusing on participants' cultural capital (Cronbach's α 0.84) and parental cultural capital (Cronbach's α 0.73) [59]. Before the experiment starts, participants will fill out a comprehensive questionnaire, which assesses level of education, occupation, income, ethnicity and participants' and participants' parental cultural capital. Since parental socioeconomic status is a strong determinant of early socialization, which affects both embodied cultural capital (taste) and institutionalized cultural capital (level of education) [23,60], parents' income, level of education and cultural capital also serve as strong indicators of participants' socio-cultural background and will therefore be assessed in this study [61,62]. Hence, socio-cultural background will be assessed using these variables: level of education (participant and parents), current occupation, income (participant and parents), and cultural capital (participant and parents). Current occupation and household income will be grouped according to the Goldthorpe class schema [63].

Additional baseline characteristics such as age, medical history and everyday music listening behavior will be evaluated. Music listening behavior will be assessed as part of the participant's cultural capital. The participant is asked about weekly hours dedicated to passive and active music listening, importance attributed to music and whether they play any instruments and/or are professional musicians. An overview of the questionnaire about background characteristics and socio-cultural background is provided in Table 2.

**Table 2 tbl2:** Overview of the questionnaire about socio-cultural background.

Questionnaire groups	Questionnaire items
General background	Age Handedness (right- or left-handed) Length and weight Earlier participation in comparable experiment(s)
Medical questions	Medical history Usage of medication Usage of alcohol Usage of drugs
Economic status	Current occupation (*participant*) Monthly income (*participant, parents*)
Cultural capital	Level of education of (*participant, parents*) Frequency of the following activities (*participant, parents*) Classical concert/opera/ballet Museum of arts Theater Cinema Dining out Pop-/rock concert Visiting sports events Night out with friends/family Hiking/biking Importance of art and culture (*participant, parents*) Importance of music Active music listening per day Passive music listening per day
Ethnicity	Country of birth (*participant, mother, father*)
	

#### Music characteristics

2.4.5

Literature indicates that different elements of music such as tempo and genre may have varying effects on MIA [46,64,65]. Our research group is interested in which music people choose to alleviate pain and how music selection is affected by socio-cultural background. Therefore, the self-chosen and researcher-chosen music will be assessed and compared with the help of Spotify® Application Programming Interface (API).

### Data management and statistical analysis

2.5

Data will be managed using Castor EDC (Ciwit B·V., Amsterdam), a certified data capture tool that includes skips, validation checks and an audit trail. This study will look at the influence of (preferred) music on MIA across different socio-cultural backgrounds (through an explorative approach. For normally distributed data, we plan to utilize a linear mixed model to analyze both the primary outcome (pain endurance) and secondary outcomes (pain intensity and unpleasantness, HRV, SAM, STAI-6). In the fixed-effects part of the model the following effects will be included: intervention, position within randomization sequence, age, TRAIT anxiety, level of education, economic capital (income), participants' cultural capital, parents’ cultural capital and ethnicity. Interaction terms such as intervention and position within randomization sequence will eventually be included using F and likelihood ratio test. In the random-effects structure we will incorporate random intercepts and a random effect of the time point of sequence. Because of the continuous measurement of HRV during each intervention the time point (within each intervention) will be included as fixed and random effect. This way, we will consider the period effect and potential carry-over effects of the cross-over study design. In the event of not normally distributed data a Friedman test will be performed instead. Moreover, subgroup analyses excluding participants with maximal pain endurance during all three interventions and non-adherence to the protocol will be performed. Data analysis will be performed using R version 4.0 or higher.

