Currently, there is no consensus about which music works best for which patient. Previous research investigated the psychophysiological effect of self-chosen music, highlighting the importance of individual preferences [20]. While research on pain (management) is increasingly sensitive for socio-cultural differences [21,22], research on MIA notably lacks consideration for socio-cultural background characteristics such as level of education, age or ethnicity. Sociological studies have established that these characteristics – cultural capital as a trait of level of education most specifically – act as key factors contributing to musical taste differentiation [[23], [24], [25], [26], [27]] and music perception [28,29]. Moreover, these factors affect musical taste patterns, which in turn are closely aligned with listening experience and social identity, in which musical taste plays a significant role as well [30,31]. For example, people who have enjoyed higher education levels are typically much more inclined to like ‘highbrow’ music such as classical or jazz [24,26], which also prescribe different behaviors – e.g. sitting, contemplation, not singing along – during listening and concerts than less ‘legitimate’ music preferences such as rap, schlager or heavy metal [32]. As a consequence, these socio-cultural background characteristics can potentially affect MIA [26,27], which is why this should be considered when investigating the therapeutic effects of music on pain.

This study aims to investigate whether the effect of (preferred) music on pain endurance remains consistent across different socio-cultural backgrounds. With this study, we will combine knowledge from different disciplines by integrating sociological methods into medical research, which could provide new perspectives on music as medicine. The MOSART study adopts a cross-over design, wherein every participant will undergo three distinct interventions in a randomized sequence: 1) self-chosen music, 2) researcher-chosen music, and 3) a neutral spoken-word podcast as a control condition. Following each intervention, participants will be subjected to increasing electric stimuli to assess changes in pain endurance.

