#### Relation between pain endurance, music and socio-cultural background

3.2.1

Previous research indicates a crucial role of socio-cultural background (level of education and cultural capital) in music taste formation and music perception [[23], [24], [25], [26], [27], [28]]. Thus, while it is clear that people with different backgrounds have different musical tastes, it is not clear to what extent the impact of music on pain endurance depends on these features. We hypothesize two contrasting possibilities.

First, we hypothesize that the impact of music largely depends on the degree to which it aligns with personal taste, as previous research indicates [18,19]. People will then respond most to the type of music they actually appreciate and benefit less from music that leaves them indifferent or even annoys them. In this scenario, music that fits participants’ taste will enhance pain endurance more than non-preferred music. If personal taste is indeed important, irrespective of the exact taste, we expect its effect to be similar across groups with different socio-cultural backgrounds. Our first hypothesis is therefore that the positive impact of self-chosen, preferred music on MIA is consistent for all participants.

Second and in contrast, if researcher-chosen music has a universal beneficial impact, then people's (socially differentiated) taste should not affect the degree to which music enhances pain endurance. In other words: the impact of taste should be absent, irrespective of one's socio-cultural background, demonstrating that some types of music are simply more effective in providing MIA than others. In this scenario, our second hypothesis is then that the positive impact of researcher-chosen music on MIA is consistent for all participants, independent of their socio-cultural backgrounds.

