### Challenges of the study

3.3

In the MOSART study, we aim to ensure a diverse study population with varied socio-cultural backgrounds. This emphasis is crucial because inclusive medical practice demands that we focus on more diverse social backgrounds, distinct from the typically prevalent highly educated Western study cohorts that have been overrepresented in prior experimental research on MIA [13]. Therefore, we are opting to employ stratification based on education level, recognizing it as one of the most important indicators for socio-cultural background. According to earlier sociological research experience, it can be challenging to include volunteers with lesser education levels in experimental studies in the Netherlands. Therefore, we are planning to expand communication strategies to reach more potential participants, especially from less- and medium-educated strata.

Another challenge can be found in the multidisciplinary aspect of this study. This study is based on collaboration among the interdisciplinary research group with researchers from the departments of anesthesiology, surgery and neuroscience, and sociology. A challenge in this collaboration is that the research methods can differ, for instance in study design and sample size. For example, to combine a manageable sample size that aligns with sociological aspects (higher sample sizes) with relatively time-demanding inclusions common in medical research (lower sample sizes), we are choosing an exploratory approach toward analyzing sociological variables. Moreover, by only including female participants, we aim to establish a more homogenous study population so that drawing valid conclusions about the effects of the socio-cultural background indicators remains feasible. This is particularly important as gender differences – especially the gender of researchers and participants – are strongly linked to pain perception [38,[76], [77], [78]]. Therefore, only female participants and researchers will be involved in this study. Finally, given that pain and music preference are multidimensional concepts, we contend that a comprehensive understanding of our research question can only be achieved by combining various disciplinary insights that are integral to the design of this research protocol.

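### The aim is whether the music effect is consistent across backgrounds, but the model commits only to main effects of background and leaves any intervention-by-background term to significance-test selection

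*Protocol article*

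**What the plan says.** The aim is given in the Background (section 1): "This study aims to investigate whether the effect of (preferred) music on pain endurance remains consistent across different socio-cultural backgrounds". Section 3.2.1 turns it into two hypotheses. The first is that "the positive impact of self-chosen, preferred music on MIA is consistent for all participants". The second is that "the positive impact of researcher-chosen music on MIA is consistent for all participants, independent of their socio-cultural backgrounds". Section 2.3.1 stratifies recruitment and randomisation by three levels of education so that these groups can be compared, and section 2.2 sets 28 participants per level.

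Section 2.5 describes a linear mixed model for the primary and secondary outcomes. It says: "In the fixed-effects part of the model the following effects will be included: intervention, position within randomization sequence, age, TRAIT anxiety, level of education". The list ends with "economic capital (income), participants' cultural capital, parents’ cultural capital and ethnicity". The next sentence deals with interactions: "Interaction terms such as intervention and position within randomization sequence will eventually be included using F and likelihood ratio test". If the data are not normally distributed, a Friedman test replaces the model.

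Section 2.5 calls the study of music across backgrounds explorative. Section 3.3 repeats this and links it to the limits on sample size: "we are choosing an exploratory approach toward analyzing sociological variables".

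**The concern.** Consistency of the music effect across backgrounds means that the difference between a music condition and the podcast does not change with background. A model speaks to that only if it crosses intervention with background. A main effect of education says whether women with more schooling tolerate more current on average over the three conditions. It says nothing about whether music helps them more or less.

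The article gives a specific list of fixed effects and names one interaction, and that interaction addresses a cross-over nuisance (order) rather than the aim. The term that would answer the aim depends on passing a significance test. Both hypotheses predict no heterogeneity, so failing the test would look like support for them. The model left after dropping the term reports one common music effect, which a reader could take as evidence of consistency although it was never estimated by stratum.

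**Working it through.** **1. What the listed model returns.** Write the endurance of participant *i* under condition *t* as a person effect, plus a condition effect, plus β × education, plus error. In the difference between self-chosen music and podcast for the same person, the education term cancels. One music effect is therefore fitted for all strata. A simulated data set shows this (28 per stratum, ICC 0.5, true music effects 0, 0.4 and 0.8 SD):
- The main-effects model gave a single effect of 0.33.
- With intervention × education added, the stratum effects were −0.12, −0.12 + 0.65 = 0.53, and −0.12 + 0.70 = 0.58. Their mean is 0.33.
- The likelihood ratio statistic was 11.9 on 4 df (p = 0.018). This is one data set and serves only as illustration.

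**2. The plan's own sample size.** Inputs from section 2.2 are d = 0.4, power 90%, two-sided 5%, and N = 84 including dropout. The ICC and dropout rate are not given, so 84 can be neither confirmed nor refuted. For one within-person contrast, with d scaled on the SD within a condition, n = 2(1 − ICC)(1.960 + 1.282)² / d².
- ICC 0.5: 10.51 / 0.16 = 65.7, so 66 (68 with the t distribution). With 20% dropout this becomes 83 (85).
- ICC 0.4: 1.2 × 10.51 / 0.16 = 78.8, so 79 (81 with t). N = 84 then allows 1 − 81/84 = 3.6% dropout.

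So 84 is reachable. The stated inputs size the overall music-versus-podcast contrast, not a difference between strata.

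**3. Power for a between-stratum difference.** The within-person difference has SD = √(2(1 − ICC)). Comparing two strata of 28, SE = SD × √(2/28), and power = Φ(0.4/SE − 1.960). The 2-df column is the test across all three strata for one contrast with effects 0, 0.2 and 0.4 SD.

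| ICC (assumed) | SD | SE | 0.4/SE | Power, two strata | Power, 2-df | Difference detectable with 90% power (SD) | n per stratum for 90% power at 0.4 SD |
|---|---|---|---|---|---|---|---|
| 0.3 | 1.183 | 0.316 | 1.26 | 24% | 18% | 1.03 | 184 |
| 0.5 | 1.000 | 0.267 | 1.50 | 32% | 24% | 0.87 | 132 |
| 0.7 | 0.775 | 0.207 | 1.93 | 49% | 38% | 0.67 | 79 |
| 0.8 | 0.632 | 0.169 | 2.37 | 66% | 54% | 0.55 | 53 |

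With 22 completers per stratum (about 20% dropout), the two-stratum power falls to about 20% at ICC 0.3 and 56% at ICC 0.8. These figures ignore period effects and the planned random effect of time point.

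**4. What the selection rule does.** A difference between strata as large as the whole effect the trial was sized on would be missed about 34% to 76% of the time (100% minus the two-stratum power) if a test decides whether it stays in the model.

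**5. The fallback.** A Friedman test ranks the three conditions within each person. It has no place for education or any other background variable, so it does not address the aim either.

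**The case against.** The strongest reply is that section 2.5 does not stop at main effects. The interaction sentence offers its term as an example, so an intervention × education term is permitted, and an F or likelihood ratio test of it would be a test of effect modification. This stands. A reader might infer that the model cannot test the aim, or that it forces one common effect on all strata. The text does not support either reading. What it supports is that the term is not named, not committed to, and subject to selection.

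Second, the background analysis is declared exploratory, with sample size as the reason. That also stands. It excuses the absence of formal power for the interaction. It does not make a main effect answer an interaction question, and it argues for estimates with intervals rather than for a significance filter.

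Third, this is a condensed article, and the full protocol or an analysis plan may list the interactions. That is possible. But the article sets out nine fixed effects, an example interaction and an inclusion rule, so the mismatch lies in what is stated.

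Fourth, a reader might infer that adding the background main effects changes the intervention contrasts by exactly zero. With complete data that holds for random intercepts alone. With the planned random effect of time point it does not. Checks with assumed variances found shifts of at most about 0.03 outcome units, which are small and unrelated to heterogeneity.

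Finally, the interaction term will not settle the aim at this sample size. That is correct and belongs in the plan.

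**Conclusion.** The concern holds in this form: the plan's aim and hypotheses are about an intervention-by-background interaction, and the stated model neither names nor commits to one. Any such term depends on a test with about 24% to 66% power for a 0.4 SD difference between two education strata. Real heterogeneity could then be removed and the pooled effect presented as consistent.

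The power range rests on an assumed ICC of 0.3 to 0.8, full strata of 28, complete data, and d scaled on the SD within a condition. The mismatch between model and aim rests on none of these.

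**What to change.** Before outcome data are compared between conditions, and with the change dated:
- Put intervention × level of education into the primary-outcome model as a term that is always retained. It uses (3 − 1) × (3 − 1) = 4 df and the existing strata.
- Report self-chosen minus podcast, researcher-chosen minus podcast, and self-chosen minus researcher-chosen in each stratum. Report their between-stratum differences too, all with 95% confidence intervals.
- Keep this labelled exploratory. Fit other interactions with intervention (cultural capital, parental cultural capital, income, ethnicity) in separate models with the same label.
- State that a non-significant interaction does not show consistency.
- For non-normal data, replace reliance on the Friedman test alone with a method that keeps the interaction, such as a transformation or a comparison of within-person differences between strata.
- If the full protocol or analysis plan already names the term, align the published wording with it.

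The cost is wording and 4 df, with no new participants or measurements. The intervals will be wide. At an assumed ICC of 0.5, a stratum-specific contrast has a 95% half-width of about 1.96 × 1/√28 = 0.37 SD, and a between-stratum difference about 1.96 × 0.267 = 0.52 SD. That width is a fair picture of what the trial can say about consistency.

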### Study design

2.1

This randomized controlled trial investigates the effect of self-chosen music and researcher-chosen music while considering socio-cultural background. Listening to a neutral, non-musical informative podcast will serve as a non-music control condition. The study will have a Latin-square crossover design to account for individual differences in pain perception and the influence of music. Hence, each participant will receive all three interventions (self-chosen music, researcher-chosen music, and control) in a randomized order. Each intervention has a duration of 20 min, and there will be a 20-min washout period between interventions. In this wash-out period, no music or stressful activities will be allowed. At the end of each intervention, pain endurance by increasing electric stimuli will be tested as the primary outcome of this study. Moreover, physiological assessments, psychological questionnaires – evaluating emotions and anxiety – and a comprehensive survey regarding socio-cultural background will be conducted. Measurements will take place at the outpatient clinic of the Center of Pain Medicine at Erasmus Medical Center, Rotterdam. See Fig. 1 for a comprehensive overview of the study design.

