### Sample size calculation

2.2

As there is currently no published research examining the interaction of music with socio-cultural background in relation to pain sensation, we conducted a power analysis based on the same meta-analysis that was used in the previous trial (CRESCENDo-trial) [5,33]. We estimated a slightly lower effect size (Cohen's d 0,4), considering the utilization of a podcast as a non-music control condition in this study. The intraclass correlation coefficient (ICC) was estimated based on a study that assessed pain intensity and unpleasantness ratings before and after listening to music [17]. To obtain a power of 90 % with a two-sided significance level of 5 % and under consideration of possible dropouts, we calculated that a sample size of 84 was needed. Thus, each group, stratified by level of education, will consist of n = 28.

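### The HRV mixed model names no participant-by-period random intercept; unless position in the sequence is a factor within participant, repeated HRV readings make the intervention test anti-conservative

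*Protocol article*

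**What the plan says.** **Design.** Section 2.1 of the protocol article describes a three-period crossover in which "each participant will receive all three interventions (self-chosen music, researcher-chosen music, and control) in a randomized order". On timing: "Each intervention has a duration of 20 min, and there will be a 20-min washout period between interventions".

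**HRV recording.** Section 2.4.2: "Heart rate variability (HRV) will be monitored continuously throughout each listening intervention and pain stimuli procedure". The article does not say how many HRV values are taken from each period.

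**Model for all listed outcomes.** Section 2.5 plans one linear mixed model for pain endurance and the secondary outcomes, HRV among them. Its fixed effects include intervention and position in the sequence. On the random part: "In the random-effects structure we will incorporate random intercepts and a random effect of the time point of sequence".

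**Addition for HRV.** "Because of the continuous measurement of HRV during each intervention the time point (within each intervention) will be included as fixed and random effect". The article adds that this is how period and possible carry-over effects are taken into account.

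**Fallback.** "In the event of not normally distributed data a Friedman test will be performed instead".

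The text does not say whether the random position effect is a factor or a linear slope, nor at what level the intercepts and the within-intervention time effect are grouped.

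**The concern.** With within-period time in the model, each period contributes several HRV rows per participant. The intervention is constant across those rows and is given to each participant once. The unit that carries information on the intervention is therefore the participant-period, 84 x 3 = 252 in all, however finely the recording is cut.

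A participant's HRV level can shift for a whole period for reasons unrelated to the average effect of the intervention, and all readings in that period then move together. The study's rationale makes some such variation likely. Section 3.2.1 considers that listeners may gain from music they like and less from music that leaves them cold, which means different participants responding differently to the same playlist.

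A participant intercept, a straight-line trend over positions 1 to 3 and a participant-level time slope cannot represent a shift confined to one period. The model then treats the shift as though it had been replicated by every reading. Standard errors for the intervention contrasts, and for any interaction of intervention with background, come out too small, and they shrink as more windows are cut. Section 2.4.2 presents HRV as an objective measure of physiological response, so a false positive would be read as evidence of an autonomic mechanism.

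**Working it through.** **Inputs from the article.** 84 participants (section 2.2); three periods, one intervention in each (section 2.1); the random effects of section 2.5. The only stated significance level is two-sided 5%, given for the sample size: "To obtain a power of 90 % with a two-sided significance level of 5 % and under consideration of possible dropouts". No error rate is stated for the HRV test, so there is no figure of the plan's own to reproduce.

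**Assumed inputs.** Readings per period m = 4, 10 or 20 (windows of 5, 2 or 1 min in a 20-min period). Ratio r of participant-by-period variance to reading-level residual variance, from 0 to 1.0. The article gives neither.

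**Step 1: which codings supply the term.** Each participant has one intervention per position, so position as a factor within participant is the same grouping as participant-by-intervention. A linear position slope within participant is not.

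**Step 2: can the factor coding serve all outcomes?** For pain endurance the repeated measurements are averaged to one value per period (section 2.4.1). A factor within participant then has 84 x 3 = 252 random effects for 84 x 3 = 252 values, and its variance cannot be separated from the residual. A linear slope does not meet this limit.

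**Step 3: approximate size without the term.** Take the residual variance as 1.
- True variance of a period mean, apart from the participant intercept: r + 1/m = (1 + mr)/m.
- The model pools, per participant, 2 between-period degrees of freedom with mean square 1 + mr and 3(m - 1) within-period degrees of freedom with mean square 1. Pooled residual: [2(1 + mr) + 3(m - 1)]/(3m - 1) = 1 + 2mr/(3m - 1).
- Factor by which the variance is understated: k = (1 + mr)/[1 + 2mr/(3m - 1)].
- A 2-df chi-square test at 5% has critical value 5.99, half of which is 2.996, so its true rejection rate is exp(-2.996/k).

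For m = 4, r = 0.25: k = 2/1.182 = 1.69 and exp(-2.996/1.69) = 17%. For m = 20, r = 0.25: k = 6/1.169 = 5.13 and exp(-2.996/5.13) = 56%. For r = 0: k = 1, giving 5%.

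**Step 4: simulation with no intervention effect**, 84 participants, 14 in each of six orders, REML fit, 2-df test at 5%.

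Simulation 1: participant intercept, linear position slope and time slope; 400 runs for m = 4 and 200 for m = 20.

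| r | m = 4, as listed | m = 4, term added | m = 20, as listed | m = 20, term added |
|---|---|---|---|---|
| 0.1 | 9.8% | 6.3% | 31.5% | 4.0% |
| 0.25 | 14.5% | 5.5% | 53.0% | 7.0% |
| 0.5 | 26.3% | 4.8% | 72.5% | 3.5% |
| 1.0 | 38.8% | 4.5% | 82.0% | 4.5% |

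Simulation 2: different variance settings (participant 0.5, residual 0.2); every model has a participant intercept and time slope; 1000 runs for m = 4 and 20, and 250 for m = 10.

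| m | r | No position effect | Linear position slope | Position as factor within participant |
|---|---|---|---|---|
| 4 | 0 | 5.2% | 5.1% | 4.9% |
| 4 | 0.25 | 18.0% | 14.9% | 5.8% |
| 4 | 0.5 | 26.8% | 23.2% | 5.0% |
| 4 | 1.0 | 35.3% | 35.5% | 5.1% |
| 10 | 0.25 | 40.0% | 36.8% | 4.8% |
| 10 | 0.5 | 53.6% | 55.6% | 4.4% |
| 20 | 0 | 5.1% | 4.7% | 4.4% |
| 20 | 0.25 | 55.7% | 54.8% | 5.6% |

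The step 3 values for r = 0.25 (17% and 56%) agree with the column without a position effect (18.0% and 55.7%). A linear slope gives little protection.

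**The case against.** A reader might infer that the planned model certainly lacks the term and will produce false HRV effects well above 5%. The documents do not support that, for three reasons.

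1. The sentence before the HRV one includes a random effect of position. As a factor within participant it is the missing term, and rejection is then 4.4-5.8% in every scenario of simulation 2. Position is a three-level design factor, and the article nowhere mentions a linear slope. The HRV time effect could also be meant as nested in intervention within participant; with its own intercept at that level it would do the same.
2. Redundancy of the factor coding for pain endurance does not prove a linear slope for HRV. For a single-value outcome only the split between that variance and the residual is unidentified; the total is estimable and the intervention test still works.
3. The inflation needs several readings per period and a non-zero participant-by-period variance. The article gives neither, and at zero variance every coding holds about 5%.

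All three stand, and they make the finding conditional. It could also be said that coding and grouping belong in an analysis plan that is not shown. That is fair for window length or the degrees-of-freedom method. It is less convincing for the random-effects structure, because the article lists that structure term by term, adds a sentence for HRV, and still does not name the one term on which the test's validity depends. The stated aim, handling period and carry-over effects, is also not the clustering of readings within a period.

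**Conclusion.** The point holds in conditional form. As listed, the HRV model names no participant-by-period random intercept, and only one unstated coding or nesting choice would supply it. The coding that can be fitted with separable variances for every listed outcome, a linear position slope, leaves the HRV intervention test anti-conservative whenever HRV level varies between a participant's periods. Under assumed ratios of 0.1 to 1.0, false positives run at about 10-39% with 4 readings and about 31-82% with 20. The lowest figure, 9.8% from 400 runs, has a standard error of about 1.5 points (square root of 0.098 x 0.902/400). The ratios and reading counts are assumptions; that inflation rises with both follows from the formula for k.

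The reach is limited. HRV is secondary. Pain endurance has one value per period and is unaffected, and the Friedman test uses one value per participant and intervention. The text should be corrected before HRV is analysed, but the main comparison is not in doubt.

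**What to change.** For HRV, state in section 2.5 a random intercept for participant-by-period (equivalently participant-by-intervention) in addition to the listed effects, for example (1 | participant/period), and test intervention with Satterthwaite or Kenward-Roger degrees of freedom.

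Alternatively, reduce HRV to one summary value per participant per intervention, analyse it with the pain-endurance model, and keep within-intervention time for describing the time course only. The Friedman fallback would need that single value anyway.

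Either change takes one sentence and at most one extra variance term in the R model, with no new data or participants. If factor coding was intended all along, the sentence only makes it explicit. The downside is wider HRV confidence intervals, which reflect the information that 252 participant-periods carry.
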